### Measures

#### Work package 1.

Parent, carer and HCP will partake in semi-structured interviews [see Additional File 1 for topic guides]. The topic guides for these interviews are designed to gather information focused on the following core areas: (1) Demographic questions about the participant and their family. (2) How did/do participants experience family-visit provision? (3) How would they improve aspects of provision (e.g., family room information provided)? (4) During family visits, what changes/actions/elements would support parents/children to: (a) Feel in control of the situation? (b) Provide positive distraction? (c) Increase family connection and opportunities for social support? (5) How could wellbeing be supported during family visits?

The interviews with children and young people will use a “draw, write, tell” approach which has been identified as facilitating involvement in interviews from children with a broad range of ages and abilities, as well as those with limited English-speaking skills [18]. The online interview approach will take the following format, which reflects the core elements of the approach developed by Angell and Angell [18]. From the outset, the interviewer will seek to build rapport with the CYP to support an effective working relationship and maximise the time together. After brief familiarisation with the drawing tools, the CYP is invited to remember their experience of visiting their parent in hospital and to draw whatever those memories made them think about. They are told they can add writing to their drawing if they wish to. They are advised that there are no right or wrong answers. Once the drawing is complete, the participant is invited to describe their drawing using open-ended questions. Questions relating to how hospital visitation could be improved for CYPs will be asked if this is not part of the above discussion. If the CYP consents, their ‘drawings’ are downloaded or captured through a screenshot.

#### Work package 2.

The brief anonymous questionnaires focus on the experience of family visits and suggested enhancements [see Additional file 1]. The questionnaire will be developed by the study team and will integrate data from Work Package 1. It will include a list of improvements/components generated in response to the findings of Phase 1. These will be developed from the point of data familiarisation onwards (see Analysis section for further information).

The questionnaire will use these items to engage with Ullrich’s [13] core elements of supportive design (control, positive distraction and social support). This will take the form of inviting participants to match specific emotions to potential enhancements: e.g., “If there were [clearer signage]/ [artwork]/ [comfortable furniture] I would feel… in control/ less anxious/ more relaxed/ more connected with my family member…”. Participants will also be asked to rank proposed improvements in order of priority. Additional items will incorporate salient concepts from environmental psychology and supportive healthcare design – e.g., reducing exposure to environmental stress [19].

This will take the form of inviting participants to match specific emotions (happy, relaxed, calm, safe, interested, energised, in control, connected to others, other) to potential enhancements (e.g., information about how to arrange/book visit).

They will also be asked to rank improvements in order of priority. This approach will facilitate validation of work package 1 findings and use a larger dataset to prioritise recommendations for enhancements generated during qualitative data collection [20].There will also be optional free text boxes for participants to provide recommended enhancement to provision – an approach which has been found to improve the quality and quantity of data related to satisfaction with services in questionnaire-based methods [21]. Face validity of the questionnaire will be assessed by the Lived Experience Advisory Panel attached to the study, and relevant stakeholders (e.g., healthcare professionals).

All items, excluding the optional free-text question, will be forced response to maximise data collection. The demographic, family background, service use/professional practice will include a ‘prefer not to answer’ option.

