#### Work package 2.

Participation can take place online; participating NHS sites can also choose to administer paper versions of the questionnaires. Online participation: following provision of the PIS and online eligibility screening, participants will provide consent using an online Qualtrics form after which they will gain access to the questionnaire. Participants will be able to download a copy of the PIS. After the completion of the online questionnaire, participants will be able to download the debrief sheet and can submit their email address through a separate Qualtrics questionnaire to win a £50 voucher.

Participation through paper version within NHS trusts: eligible participants will be provided with a physical copy of the PIS and provide consent with a paper version of the ICF, then they will be provided with the paper version of the questionnaire. Participants will then be provided a copy of the debrief sheet and asked whether they want to submit their email to win a £50 voucher.

Staff will collect, scan and then securely destroy the paper ICF and questionnaires, scanned copies will be sent to the research team through the encrypted NHS email service. Staff will submit the email addresses of participants wanting to take part in the prize draw to the relevant Qualtrics questionnaire. Research staff will enter questionnaire answers into the Qualtrics data, scans of the ICFs will be stored on a secure University of Sussex server.

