#### Work package 2.

All analysis will be conducted using SPSS and/or R(Studio). Quantitative analysis will be descriptive in nature, as the study is exploratory and not powered for inferential statistics. Descriptive statistics will be used to summarise the demographics and questionnaire responses, specifically: (1) Frequencies and percentages will be reported for categorical variables (e.g., endorsement of each emotion linked to environmental enhancements). (2) Means, medians, and standard deviations will be used to summarise continuous or ordinal variables (e.g., average ranking positions of enhancements). (3) For the ranking exercise, mean rank scores will be calculated alongside frequency counts of “top five” selections, to provide indications of both central tendency and practical salience. (4) Subgroup trends (parents, carers, HCPs) will be described but not subjected to hypothesis testing.

Free-text qualitative data will be incorporated into the above framework analysis (work package 1) in NVivo and used to generate a word cloud. Analysis will be conducted by the research team, including lived experience researchers.

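### Work package 2 forces an answer to every emotion item but lists no 'no difference' or negative choice, so endorsement percentages risk upward bias of unknown size; the rule also cannot hold on paper forms

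*Protocol article*

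**What the plan says.** The protocol article, Measures, Work package 2, sets the response rule: "All items, excluding the optional free-text question, will be forced response to maximise data collection". The next sentence gives the only stated opt-out: "The demographic, family background, service use/professional practice will include a ‘prefer not to answer’ option". Nothing similar is stated for the items on enhancements.

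The same section asks respondents to "match specific emotions (happy, relaxed, calm, safe, interested, energised, in control, connected to others, other) to potential enhancements". The illustrative item stem also runs only towards improvement: "I would feel… in control/ less anxious/ more relaxed/ more connected with my family member". The section adds that matching and ranking together will help to validate the work package 1 findings and to prioritise recommendations.

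The Analysis section for work package 2 plans the summary: "Frequencies and percentages will be reported for categorical variables (e.g., endorsement of each emotion linked to environmental enhancements". Ranking is summarised separately by mean ranks and counts of top-five selections. All of it is descriptive, with no hypothesis tests.

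The Procedures section for work package 2 says that "participating NHS sites can also choose to administer paper versions of the questionnaires". Research staff then key the answers into the Qualtrics data. The Amendments table dates paper questionnaires and a new questionnaire version to 10 June 2026 (version 2.5).

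**The concern.** Taken together, these statements leave a respondent who thinks an enhancement would do nothing, or would make a visit worse, without a fitting answer. That person cannot skip the item and cannot say 'no difference'. The choice is between a positive emotion that is not felt and 'other'.

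At stake is what the endorsement percentages can mean. If no null answer can be recorded, the emotion items cannot contradict a component from work package 1, yet the article gives validation of those findings as one purpose of the questionnaire. Ranking does not fill this gap, because it gives relative order only: an enhancement ranked last may still help, and one ranked first may help few. The results go on to inform the co-production of the Family Visit Pack.

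A smaller matter is that a paper form cannot enforce a response, so the universal wording of the rule conflicts with the paper mode that the same article allows.

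**Working it through.** **The plan's own figure.** The only figure nearby is the work package 2 sample size (Sample size section): 50 parents + 25 carers + 25 healthcare professionals = 100, which reproduces. The point disputes no stated number. No power or alpha formula applies, because the analysis is descriptive.

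**Options as listed.** "happy, relaxed, calm, safe, interested, energised, in control, connected to others, other" comprises eight positive states and one residual. There is no null, negative or opt-out choice.

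**Size of the possible bias.** The documents give no input for this, so the values below are assumptions.

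- q = share of respondents who expect no benefit from a given enhancement
- p = 1 − q = share who would truly feel some positive emotion
- f = share of the no-benefit respondents who choose 'other'

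Observed share with any positive emotion = p + (1 − p)(1 − f).

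Bias = observed − p = q(1 − f).

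The plan reports "endorsement of each emotion linked to environmental enhancements", that is, each emotion separately. If each respondent makes one choice and the forced answers spread evenly over the eight emotions, each emotion gains q(1 − f)/8.

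| q | f | True any-positive | Observed | Bias (points) | Per emotion (points) |
|---|---|---|---|---|---|
| 10% | 0 | 90% | 100% | 10 | 1.25 |
| 10% | 50% | 90% | 95% | 5 | 0.62 |
| 10% | 100% | 90% | 90% | 0 | 0 |
| 20% | 0 | 80% | 100% | 20 | 2.5 |
| 20% | 50% | 80% | 90% | 10 | 1.25 |
| 20% | 100% | 80% | 80% | 0 | 0 |
| 40% | 0 | 60% | 100% | 40 | 5 |
| 40% | 50% | 60% | 80% | 20 | 2.5 |
| 40% | 100% | 60% | 60% | 0 | 0 |

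The bias is never negative and never exceeds q. The article does not say whether items are single- or multi-select. If forced answers bunch on one emotion, or if several may be ticked, the gain for one emotion can exceed the last column, but it remains bounded by q(1 − f).

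**Whether the data could reveal f.** They could not. The 'other' count mixes 'no difference', 'worse' and positive feelings that are not listed, so it cannot be read as the share without benefit.

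**Paper forms.** Let s be the share of forms on paper and b the share of blank answers to an item on those forms, both assumed. Answers available = N(1 − s·b).

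- s = 10%, b = 5%: 100 × (1 − 0.005) = 99.5 of 100, and 25 × 0.995 = 24.9 of 25.
- s = 50%, b = 20%: 100 × (1 − 0.10) = 90 of 100, and 25 × 0.90 = 22.5 of 25.

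The item denominator is therefore not guaranteed to equal the number of respondents, as a universal forced response would imply.

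**The case against.** The strongest reply is that 'other' is a listed option, so nobody is compelled to record a positive emotion. That stands. A reader might infer that the percentages are inflated by construction, but the documents do not support this: the bias may be zero.

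A reader might also assume that no-benefit respondents choose evenly among all nine options. Then q × 8/9 gives a spurious positive answer from 18%, 36% or 53% of respondents at q = 20%, 40% or 60%. That figure makes 'other' no likelier than any other option for the very people it fits best. It also assumes single choice and adds up eight emotions that the plan reports separately. On the same assumption each emotion gains q/9, or 2.2, 4.4 and 6.7 points.

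It can be said further that prioritisation rests on the ranking exercise, that free-text boxes exist, and that a Lived Experience Advisory Panel and stakeholders assess face validity. The ranking part stands: mean ranks and top-five counts do not use the emotion list, so it would be wrong to say that work package 2 cannot discriminate between components. Endorsement is also only an example of a categorical variable in the Analysis section, not a designated first outcome. The other safeguards may catch the problem but do not supply a null answer.

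A reader might suspect that partial paper rankings distort the mean ranks. Dropping unranked items lowers the means of items generally. In one simulation (15 items, paper forms ranking only five, 30% or 50% on paper, all assumed), an item loved by 25% moved from 9.2 to 8.3 or 7.4. The other items averaged 7.9, 7.3 and 6.7, and the niche item stayed last. Under another assumed preference model the gap to a broadly liked item shrank from 1.7 to 0.5 ranks, again without reversal. Some compression is possible, but none of these inputs is in the documents, and top-five counts are untouched in that scenario. The coding of blank paper items is mostly a detail that an article leaves to fuller documents.

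The lack of an explicit positive-distraction option is a matter of preference, since 'interested' may stand for it.

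Finally, the questionnaire in Additional file 1 is not shown and may hold a neutral option or a text field. That is a real limit. The article nevertheless states the rule, the scope of the opt-out and the option list, so the point disputes stated choices, not an omission.

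**Conclusion.** The concern holds in a limited form. As written, the emotion items give respondents who expect no benefit or a worse visit no interpretable answer. The endorsement percentages are at risk of upward bias, anywhere from zero to the full no-effect share, and the planned data cannot show where in that range they lie. This limits the use of the emotion items to validate work package 1. It does not touch the ranking or top-five results, and no test is affected because there is none.

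The universal forced-response statement conflicts with the paper mode; that needs a correction of wording and clear denominators.

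The conclusion rests on the article's option list being complete. The sizes rest on assumed no-effect shares of 10% to 40% and, per emotion, on single choices spread evenly. In a descriptive, exploratory survey this is a cheap improvement, not a must-fix.

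**What to change.** 1. Add 'would make no difference / none of these' and 'would make it worse' to each emotion item. If the questionnaire in Additional file 1 already has them, correct the description in Measures, Work package 2 instead.
2. Report the 'no difference' percentage beside each endorsement percentage.
3. Limit the forced-response statement to the online version.
4. Record mode (online or paper) and show item denominators by mode.

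Cost: a questionnaire amendment, whose category the sponsor decides under the article's own procedure, and a little extra tabulation. Responses collected before the change must be flagged by questionnaire version and their endorsement percentages shown separately. Work package 2 data collection runs from June to 30 November 2026, so an early change helps most: a null answer that was never offered cannot be recovered at analysis.

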### Analysis

#### Work package 1.

The analysis will be conducted to meet two objectives: 1) to describe participants’ experiences of hospital visitation; 2) to generate a list of potential components/enhancements for provision to incorporate into the questionnaire deployed in work package 2, which will be used in subsequent co-design work.

Interviews will be transcribed by the research team, and subject to a five-stage framework analysis (in NVivo) which involves familiarisation, theme identification, indexing (the application of themes onto transcripts), charting and summarising using a matrix, and finally interpretation/mapping. This analytical approach is well-suited to the project’s research objectives, as it is flexible; can accommodate large and relatively non-homogenous datasets, including those from varied participant types; and enables the inclusion of themes developed from the data alongside a priori concepts (e.g., suggested environmental improvements to enhance control, positive distraction and connection). The list of components for work package 2 will be generated during the familiarisation and theme identification stages, which will facilitate timely progression into work package 2 data collection. Transcription and analysis will occur concurrently with data collection to expedite generating the results. Analysis will be carried out by the research team and lived experience researchers will inform and review the analysis throughout.

#### Work package 2.

All analysis will be conducted using SPSS and/or R(Studio). Quantitative analysis will be descriptive in nature, as the study is exploratory and not powered for inferential statistics. Descriptive statistics will be used to summarise the demographics and questionnaire responses, specifically: (1) Frequencies and percentages will be reported for categorical variables (e.g., endorsement of each emotion linked to environmental enhancements). (2) Means, medians, and standard deviations will be used to summarise continuous or ordinal variables (e.g., average ranking positions of enhancements). (3) For the ranking exercise, mean rank scores will be calculated alongside frequency counts of “top five” selections, to provide indications of both central tendency and practical salience. (4) Subgroup trends (parents, carers, HCPs) will be described but not subjected to hypothesis testing.

Free-text qualitative data will be incorporated into the above framework analysis (work package 1) in NVivo and used to generate a word cloud. Analysis will be conducted by the research team, including lived experience researchers.

#### Status and timeline of the study.

Recruitment for the project began on 03^rd^ March 2026 with data collection continuing until 30^th^ November 2026. Recruitment and data collection for WP1 will run from March 2026 to August 2026 and recruitment and data collection for WP2 will run from June 2026–30^th^ November 2026. It is expected that results will be completed by February 2027. See Table 2. for SPIRIT Timeline

**Table 2 pone.0355693.t002:** SPIRIT participant timeline.

WORK PACKAGE 1: QUALITATIVE INTERVIEWS					
	**ENROLMENT**		**DATA COLLECTION**		**CLOSE-OUT**
**TIMEPOINT**	**−t_1_**	**0**	**t_1_**	**t_2_**	**tₓ**
**ENROLMENT**					
Expression of interest	X				
Eligibility screening	X				
Introductory discussion	X				
Capacity assessment*	X				
Informed consent/ assent		X			
**ASSESSMENTS**					
Demographic information			X		
Semi-structured interview			X		
Debrief discussion^^^					X
Debrief information sheet					X
Study summary (optional)					X
**WORK PACKAGE 2: QUESTIONNAIRE**					
	**ENROLMENT**		**DATA COLLECTION**		CLOSE-OUT
**TIMEPOINT**	**−t_1_**	**0**	**t_1_**	**t_2_**	**tₓ**
**ENROLMENT**					
Participant Information Sheet	X				
Eligibility screening	X				
Informed consent		X			
**ASSESSMENTS**					
Demographic information			X		
Questionnaire			X		
Debrief information					X
Prize draw entry (optional)					X

* Capacity assessment where applicable. ^Optional.

## Discussion

This study aims to address a significant gap in understanding the experiences of families when a parent is admitted to psychiatric inpatient care. By incorporating perspectives from parents, children and young people, carers, and healthcare professionals, the study seeks to generate a comprehensive understanding of current provision and priorities for improvement, which will inform the co-production of a ‘Family Visit Pack’ of guidance principles and environmental enhancements designed to improve visits.

This study will recruit participants from the community (e.g., social media, communities of interest, and charities) and five collaborating NHS sites. Consequently, the findings may not fully capture experiences across other NHS sites, private mental health settings, or across demographic groups.

On completion of the study, the data will be analysed and tabulated and a Final Study Report prepared for REC and Sponsor. A final accessible lay study report will be produced and published on the study website and shared with participants who wish to receive it. Reporting of study findings will use the appropriate guidelines as identified from the EQUATOR network (https://www.equator-network.org/).

### Amendments

**Table pone.0355693.t003:** 

*Protocol version no.*	*Date issued*	*Author(s) of changes*	*Details of changes made*
*2.1*	*13 Feb 26*	*CI*	Inclusion of demographic questions on CYP topic guide; inclusion of geographical identifier (county) on adult topic guides and questionnaires; general (all groups) recruitment poster./
*2.1*	*24 March 26*	*CI*	An additional data field requesting information about which county the participant resides in has been added to the online questionnaire used for all WP2 participants
*2.1*	*25 March 26*	*CI*	Addition of new site: Somerset Foundation NHS Trust.
*2.4 (2.2 and 2.3 related to non-agreed changes which were incorporated into v 2.4*	*28 April 26*	*CI*	Addition of new sites: North staffs and Lincolnshire
*2.5*	*10 June 26*	*CI*	Paper questionnaires and new questionnaire version
